## LIST OF ABBREVIATIONS AND RELEVANT DEFINITIONS

|                   |                                                                                                                                                                                                                                                                                                                                                  |
|-------------------|--------------------------------------------------------------------------------------------------------------------------------------------------------------------------------------------------------------------------------------------------------------------------------------------------------------------------------------------------|
| 95% CI     | 95% confidence interval                                                                                                                                                                                                                                                                                                                   |
| AE         | Adverse Event                                                                                                                                                                                                                                                                                                                             |
| CISS       | Cold Intolerance Symptoms Severity score                                                                                                                                                                                                                                                                                                  |
| CPSC       | Consumer Product Safety Commission                                                                                                                                                                                                                                                                                                        |
| CRF        | Case Report Form                                                                                                                                                                                                                                                                                                                          |
| DSMB       | Data Safety Monitoring Board                                                                                                                                                                                                                                                                                                              |
| ED         | Emergency Department                                                                                                                                                                                                                                                                                                                      |
| EQ-5D-3L   | EuroQoL-5D-3L                                                                                                                                                                                                                                                                                                                             |
| EudraCT    | European drug regulatory affairs Clinical Trials                                                                                                                                                                                                                                                                                          |
| GP         | General Practitioner                                                                                                                                                                                                                                                                                                                      |
| HEMS       | Helicopter Emergency Medical Services                                                                                                                                                                                                                                                                                                     |
| HUI-3      | Health Utilities Index                                                                                                                                                                                                                                                                                                                    |
| ICU        | Intensive Care Unit                                                                                                                                                                                                                                                                                                                       |
| LEFS       | Lower Extremity Functional Scale                                                                                                                                                                                                                                                                                                          |
| METC       | Medisch Ethische Toetsing Commissie (METC); in English: Medical Research Ethics Committee (MREC)                                                                                                                                                                                                                                          |
| MREC       | Medical Research Ethics committee (MREC); in Dutch: Medisch Ethische Toetsing Commissie (METC)                                                                                                                                                                                                                                            |
| NTR        | Nederlands Trial Register (in English; Netherlands National Trial Register)                                                                                                                                                                                                                                                               |
| POSAS      | Patient and Observer Scar Assessment Scale                                                                                                                                                                                                                                                                                                |
| Quick-DASH | Quick Disabilities of Arm, Shoulder and Hand score                                                                                                                                                                                                                                                                                        |
| SD         | Standard Deviation                                                                                                                                                                                                                                                                                                                        |
| Sponsor    | The sponsor is the party that commissions the organisation or performance of the research, for example a pharmaceutical company, academic hospital, scientific organisation or investigator. A party that provides funding for a study but does not commission it is not regarded as the sponsor, but referred to as a subsidising party. |
| SPSS       | Statistical Package for the Social Sciences                                                                                                                                                                                                                                                                                               |
| STROBE     | STrengthening the Reporting of OBservational studies in Epidemiology                                                                                                                                                                                                                                                                      |
| SUSAR      | Suspected Unexpected Serious Adverse Reaction                                                                                                                                                                                                                                                                                             |
| TBSA       | Total Body Surface Area                                                                                                                                                                                                                                                                                                                   |
| VAS        | Visual Analogue Score                                                                                                                                                                                                                                                                                                                     |
| Wbp        | Personal Data Protection Act (in Dutch: Wet Bescherming Persoonsgegevens)                                                                                                                                                                                                                                                                 |
| WMO        | Medical Research Involving Human Subjects Act (in Dutch: Wet Medisch-wetenschappelijk Onderzoek met Mensen)                                                                                                                                                                                                                               |

## SUMMARY

**Rationale:** Fireworks-related injuries frequently occur in both adults and children. It often entails serious and avoidable injuries to innocent bystanders. Most injuries are non-fatal but a substantial amount results in life-long disabilities affecting quality of life and the use of public health services. Currently, reliable data about the affected patients, their injury characteristics, the direct and indirect costs resulting from their injury and the loss of quality of life outcomes in the long-term is lacking.

**Objective:** The main aim is to provide detailed information about the injury characteristics of patients reporting to a hospital with fireworks-related injuries. Secondary aims are to determine the treatment (and associated direct medical and indirect societal costs), clinical and functional outcome.

**Study design:** Multicenter, prospective, observational case series

**Study population:** All patients (no age limit) with fireworks-related injuries occurred between December 1, 2017 and January 31, 2018 are eligible for inclusion.

**Intervention (if applicable):** Not applicable

**Main study parameters/endpoints:** The main outcome measures are the injury characteristics. The secondary outcomes are 1) the number and type of operations needed; 2) the duration of hospital admission; 3) the direct medical and indirect societal costs; 4) the absence from school; 5) the quality of life (EuroQol-5D-3L; EQ-5D-3L) and injury specific outcomes (Health Utilities Index 3; HUI-3 (domains vision and dexterity), visual acuity, *Quick* Disabilities of Arm, Shoulder and Hand (*Quick*-DASH); Cold Intolerance Severity Scale (CISS); Lower Extremity Functional Scale (LEFS); Patient and Observer Scar Assessment Scale (POSAS); 6) patient satisfaction with their functional recovery and cosmesis; and 7) how the trauma affected patient's view on the use of consumer fireworks.

**Nature and extent of the burden and risks associated with participation, benefit and group relatedness:** The clinical follow-up program including outpatient department visits, physical examination, and diagnostics is not influenced by this study. At three, six and 12 months after presentation, adult patients and parents of pediatric patients will be asked to complete the quality of life questionnaires and the injury specific questionnaires. The investigation and completion of questionnaires will take approximately 20 minutes per visit. No other inconvenience associated with participation is expected. The risks associated with participation can be considered negligible and the burden can be considered minimal. The study could not be conducted without the participation of pediatric patients.

## 1. INTRODUCTION AND RATIONALE

Fireworks are used for celebrating all kinds of rituals and events worldwide. Despite their nice visible and audible effects, it has the potential to cause serious injuries.

Fireworks-related injuries occur frequent in both adults and children. It can be considered a public health problem as they often entail serious and avoidable injuries and often affect innocent bystanders (1-3).

In the USA, the Consumer Product Safety Commission (CPSC) presented a report stating that in 2015 approximately 12,000 fireworks-related injuries were treated in Emergency Departments (ED), reflecting an annual incidence rate of 3.7 per 100,000 individuals. Most patients were males (61%) and 42% were younger than 20 years of age (4). This is comparable with the results of several other studies (1-3, 5-9).

The percentages presented by the CPSC are comparable with the Netherlands with an incidence rate of 2.8 per 100.000 individuals per year treated at an ED with fireworks-related injuries(8). In 36% of the cases, victims were younger than 20 years of age and 76% were males. In the past ten years the number of fireworks-related injuries fluctuates between 400 and 1,000 cases annually. A clear up or downward trend is not observed in the past decade (8).

In two-thirds of all patients, the injuries are located at the hands, face and eyes, mostly consisting out of burns, superficial injuries, and open wounds (2, 5-8, 10, 11).

Most firework-related injuries are non-fatal but they do have the potential to result in long-term disability (3, 5, 8, 10). This has a great effect on the individuals' quality of life and the use of public health services, with high direct medical and indirect societal costs. A Dutch report published in 2016, calculated that the direct medical costs of an individual visiting the ED/admitted to the hospital with a fireworks-related injury are on average €1.600 per individual, based on the years 2011 – 2016, with annual costs of around €1.1 million. When the indirect costs due to absence from work are included as well, this estimate rose to €8.100 per individual and to €2.9 million annually (8).

The fireworks-related injuries in the Netherlands are concentrated around the night of New Years' Eve. Every year the fireworks-related injuries are recorded by the Dutch Society of Ophthalmology, Dutch Association of Plastic Surgeons and the Dutch Trauma Society. Since 2004, also a nationwide estimation on the number of fireworks-related injuries is made by the Consumer Safety Institute (2, 8). However, this number is an estimation based on a sample of Dutch hospitals. Detailed information about patient and injury characteristics, medical and societal costs and long-term functional outcomes are lacking. This kind of information aids the public debate and contributes to the political decision on whether or not to abolish the use of consumer fireworks.

Fireworks-related injuries are relatively easy to prevent and therefore a relevant public health problem. However, detailed knowledge is lacking on the treatment, functional impairment, and medical and societal costs on the long-term. This study aims to provide detailed information regarding patient, injury, and treatment characteristics, medical and societal costs, and patient-reported outcomes, with a follow-up of one year.

## 2. OBJECTIVES

### Primary Objective:

To determine the **injury characteristics** of fireworks-related injuries in patients reporting to a hospital for treatment.

### Secondary Objective(s):

- 1) To determine the **number and type of operations** needed due to fireworks-related injuries until one year after trauma
- 2) To determine the **duration of hospital admission** in these patients
- 3) To determine the **direct medical costs** and the **indirect societal costs (incl. work absence)** in these patients
- 4) To investigate the **absence from school** in these patients
- 5) To investigate the **patient-reported outcomes** in these patients
  - EuroQol-5D (EQ-5D-3L)
  - Health Utility Index Mark 3 (domains for vision and dexterity) (HUI-3)
  - *Quick* Disabilities of the Arm, Shoulder and Hand (*Quick*-DASH)
  - Cold Intolerance Symptoms Severity (CISS)
  - Lower Extremity Functional Scale (LEFS)
  - Patient and Observer Scar Assessment Scale (POSAS)
  - Patient satisfaction with the functional recovery and cosmesis
- 6) To investigate how the injury changed **patient's view on the use of fireworks**

### 3. STUDY DESIGN

This study will be a multicenter, prospective, observational case series.

## 4. STUDY POPULATION

### 4.1 Population (base)

All patients (no age limit) with fireworks-related injuries presenting to a hospital in the period between December 1, 2017 and January 31, 2018 in the Trauma Region Southwest Netherlands, will be eligible for inclusion. Patients will be recruited from every hospital in the Trauma Region Southwest Netherlands. In the Netherlands it is only permitted to lit fireworks as a consumer during the celebration of New Year's Eve and logically most fireworks-related injuries occur during that night or the period close before and after. Therefore, this specific time range was chosen.

### 4.2 Inclusion criteria

In order to be eligible to participate in this study, a subject must meet all of the following criteria:

- 1) Patients with any injury caused by fireworks treated\* in a hospital in the Trauma Region Southwest Netherlands between December 1, 2017 and January 31, 2018
- 2) Provision of informed consent

\* Treatment is defined as any intervention for which  $\geq 1$  clinical follow-up visit is scheduled

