### 4.3 Exclusion criteria

A potential subject who meets any of the following criteria will be excluded from participation in this study:

- 1) Patients who died within the first 24 hours due to other injuries than fireworks
- 2) Patients with incomplete or unknown contact information;
- 3) Insufficient understanding of Dutch or English to understand the study documents

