#### Treatment characteristics to be collected:

- Prehospital transport (ambulance, Helicopter Emergency Medical Services (HEMS), self-transport, other (text), or unknown)

- HEMS assistance (yes, no, or unknown)
- Referral to hospital (direct or indirect (general practitioner, general practice center, other hospital, or other (text)))
- Admission (yes or no)
- Required care (ward, Intensive Care Unit (ICU), observatory, or other)
- Wound treatment (wound dressings (text), topical therapy (text), other (text), unknown, or not needed)
- Number of transfusions required (packed-cells, platelets, plasma, colloid, or other (text description))
- Discharge destination (home, other hospital, nursing home, rehabilitation facility, burn center, or other)
- Need for prosthesis (yes or no, and description)

Outcome-related variables to be collected:

- Time between initial injury and hospital presentation (calculated from dates of trauma and hospital presentation)
- Duration of hospital admission (calculated from date of admission and date of discharge)
- Duration of ICU admission (in days) (calculated from dates of admission and discharge)
- Mortality (fireworks-related, yes or no)
- Rehabilitation (physical therapy, hand therapy, ergotherapy, other (text description), or multiple)
- Complications and secondary interventions (text description)

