### 11.3 Objection by minors or incapacitated subjects (if applicable)

Pediatric patients are involved in this study. Should pediatric patients show any sign of objection, they will not undergo examination of scar tissue quality.

Adult patients will only be enrolled if they are able to provide informed consent themselves. They cannot be incapacitated.

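### The stated population is everyone presenting to a hospital, but the entry rule keeps only consenting patients with a planned follow-up visit, and the plan has no check that would show this selection by severity

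*Protocol*

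**What the plan says.** **Target.** The Summary gives the main aim as describing the injuries of "patients reporting to a hospital with fireworks-related injuries". Section 4.1 makes eligible "All patients (no age limit) with fireworks-related injuries presenting to a hospital in the period between December 1, 2017 and January 31, 2018" within the trauma region. The primary objective in section 2 is slightly narrower: the injury characteristics "of fireworks-related injuries in patients reporting to a hospital for treatment".

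**Entry.** Section 4.2 asks for informed consent and for an injury treated in a hospital of the region. An asterisk on the word for treated leads to a footnote: "Treatment is defined as any intervention for which" one or more clinical follow-up visits have been planned.

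**Expected number.** Section 4.4 starts from 574 patients nationally, raises this to 638 for the two-month window, notes that the region has 10 of 90 hospitals, and arrives at 70-80.

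**Consent and death.** Under section 11.2 the consent visit takes place within two weeks of presentation, and parents take part for children. Section 11.3 says: "Adult patients will only be enrolled if they are able to provide informed consent themselves". Section 4.3 excludes deaths in the first 24 hours only where the cause was something other than fireworks. Section 8.1.3 lists as an outcome variable "Mortality (fireworks-related, yes or no".

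**Check on representativeness.** Section 10.3 compares participants with non-participants on gender, injury location and age.

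**The concern.** The primary outcome (section 8.1.1) is a list of injury characteristics, reported under section 10.1 as counts, percentages, means or medians. No contrast is tested, so the choice of denominator is the result. If the target is everyone who presents and the data come only from those called back, the percentages answer a different question from the one stated.

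The patients lost are unlikely to be a random subset. Section 1 names superficial injuries among the common types, and section 8.1.1 codes soft tissue damage as superficial or deep. People seen once and sent home plausibly sit mostly in the superficial category.

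Sections 1 and 10.4 say the findings are meant to inform public debate and may be released before follow-up ends. A profile tilted towards severe injury could therefore be read as the profile of all hospital presenters.

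**Working it through.** **1. Does the projection match section 4.1 or section 4.2?**

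- National figure: 574 × 1.10 = 631.4, while 574 / 0.90 = 637.8, which rounds to the stated 638. The second route gives the protocol's number exactly.
- Regional share: 638 × 10/90 = 70.9 (or 631.4 × 10/90 = 70.2). This is the low end of 70-80. No stated input gives 80, although the increase is described as a minimum.
- No factor is applied for a planned follow-up visit or for consent. The 70-80 therefore corresponds to the population of section 4.1, not to that of section 4.2.

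Let f be the share of presenters with a planned visit and c the share who consent. Neither is in the protocol. As an illustration:

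- 70.9 × f = 21 (f = 0.3), 35 (0.5), 50 (0.7) and 64 (0.9).
- With c from 0.5 to 0.9, 70.9 × f × c runs from 70.9 × 0.3 × 0.5 = 11 to 70.9 × 0.9 × 0.9 = 57.

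**2. Which way does the profile move?**

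Let s be the severe share among all presenters, m the share of mild cases with a planned visit, and q the share of severe cases lost through death, incapacity or non-consent. Assume that every severe case has a planned visit. Then

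severe share among those enrolled = s(1 − q) / [s(1 − q) + (1 − s)m].

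This exceeds s exactly when 1 − q > m, that is, when severe cases are more likely to be enrolled than mild ones. All inputs below are assumptions.

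| s | q | m = 0.3 | m = 0.5 | m = 0.7 |
|---|---|---|---|---|
| 0.10 | 0 | 0.270 | 0.182 | 0.137 |
| 0.10 | 0.2 | 0.229 | 0.151 | 0.113 |
| 0.20 | 0 | 0.455 | 0.333 | 0.263 |
| 0.20 | 0.2 | 0.400 | 0.286 | 0.222 |
| 0.30 | 0 | 0.588 | 0.462 | 0.380 |
| 0.30 | 0.2 | 0.533 | 0.407 | 0.329 |

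Example: s = 0.20, m = 0.3, q = 0 gives 0.20 / (0.20 + 0.24) = 0.455. With q = 0.1 it is 0.18 / (0.18 + 0.24) = 0.429.

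So an assumed 20% becomes 26% to 45% without severe losses, and 22% to 43% if 10-20% of severe cases are lost.

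**3. What happens at the severe end?**

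- Section 4.3 does not exclude fireworks deaths, and section 8.1.3 lists them, so they are meant to be counted.
- Consent is compulsory (4.2), may be signed up to two weeks after presentation (11.2), and for adults must be personal (11.3). No proxy or deferred route for adults is described.
- Hence an adult who dies or stays incapacitated before consent is not recorded. An adult who consents and dies later is recorded, and children can enter through their parents.

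**4. Would section 10.3 reveal this?**

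Injury location may catch some of it. Severity, admission and death are not compared, and the section does not say whether presenters without a planned visit count as non-participants.

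**The case against.** The best defence is structural. Section 4.1 is a base population, and later criteria normally narrow a base. Section 2 already speaks of patients who come for treatment. The criteria are stated openly, and section 11.2 lets people who refuse only the questionnaires consent to use of their files. This has some force for section 2, which conflicts only with the unusual definition of treatment. It does not help the Summary or section 4.1, which call all such patients eligible, nor section 4.4, whose count has no matching reduction. File-only consent does not bring back a patient who had no planned visit.

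A reader might also infer stronger points that the protocol does not support:

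- **That fireworks deaths are zero by design.** No criterion excludes them. The loss is limited to adults who die before consenting, and section 1 says most of these injuries are not fatal. Mortality after enrolment can still be observed, so there is no reason to drop the variable.
- **That every patient must consent personally.** This holds for adults only.
- **That the contact and language exclusions in section 4.3 needlessly remove patients from a file-based outcome.** File data are collected after signed consent (8.3B), and consent itself needs contact details and understanding of the study documents.
- **That section 10.3 compares only patients with planned follow-up.** Its word for treated carries no asterisk, and section 8.3A registers each patient with a fireworks injury, so non-participants may include single-visit patients. The text leaves this open.
- **That mean costs will be set against the EUR 1,600 in section 1.** That figure is background, and no such comparison is planned.

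**Conclusion.** The contradiction over the primary-outcome population stands. Followed as written, the plan would present a consenting group selected on planned follow-up as the injury profile of hospital presenters. The likely direction is too many severe injuries. This rests on the assumption that severe cases are more likely than mild ones to be both called back and enrolled.

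The size is unknown, because the protocol gives neither the follow-up share nor the consent share. It is tempting to quote a single inflation factor of 1/f, but that applies only to features that always lead to follow-up, and it ignores losses at the severe end. The figures above are illustrations, not estimates.

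The two ends are unequal. The mild end is removed by an explicit rule. The adult severe end is thinned indirectly, probably by few patients, since adults who regain capacity before the consent visit can still enter.

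**What to change.** Reconcile the Summary and sections 2, 4.1, 4.2 and 4.4 so that they name one population, by one of two routes:

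- **(a) Where permitted, report the primary profile for all presenters.** Collect body site and injury type as an unidentified count per hospital, building on the registration and registry search in section 8.3A. Keep the planned-visit criterion for the questionnaire and cost cohort.
- **(b) Restate the target.** Word the objective, section 4.1 and the section 4.4 projection as consenting patients with a planned follow-up visit. Report the number of other presenters and of deaths per hospital, and label mortality as observed after enrolment.

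Under either route, add admission (yes/no) and death to the section 10.3 comparison, and state that non-participants include presenters without a planned visit.

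Route (a) costs a short count sheet per hospital, because the registry search is currently only a completeness check. It also depends on permission to use such counts, which the protocol does not settle. Route (b) costs wording, simple counts and a narrower conclusion. The choice should be made before any early release of injury characteristics under section 10.4.
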